### **b) Orientation**

Participants and/or carers (as available) requested by therapist to bring memoir materials such as framed photographs of family and friends, photo album, music device, reading materials, pillowcase/blanket, for bedside.

### **c) Enhanced assessment**

1. Assessment of pain with the Algoplus dementia friendly pain scale from the first therapist contact and all contacts going forward.
2. Assessment of depression by the therapist using the Cornell Scale for Depression in Dementia. This should only be completed for participants with no prior depression diagnosis. The scale has two parts - one to be responded to by the participant's carer and the second by the participant themselves. The scales require responses based on 'the last week'. This should be completed following the first week in hospital. If the final score suggests a probable/definite major depression, notify multidisciplinary team, and suggest psychiatry referral.
3. The therapist will determine whether the participant has an advanced care plan (from medical chart/medical team). If there is no advanced care plan in place, refer to specialty who is responsible for supporting creation of an advanced care plan e.g. general practitioner following discharge
4. Prior to participant discharge. Ensure handover of pain history, depression assessment, and whether a new advanced care plan was established, to community team.

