## **7.4 Randomisation procedures**

The randomisation approach was designed with a statistician (SA) and validated for use prior to implementation. Once a participant has provided informed consent, they will be allocated a participant identification number (PID). Baseline data will subsequently be collected by the research team prior to randomisation. Randomisation will follow a 1:1 random allocation sequence stratified by subgroup assignment (low-, medium-, high- risk), using a secure internet-based system, developed and maintained by King's Clinical Trials Unit to ensure allocation concealment. Treatment allocation will be revealed (after randomisation) to a member of the research team, linked to the participant number, and the clinical team will be notified.

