### **a) Education**

1. Participants provided with information pack detailing what to expect from rehabilitation and their recovery.
2. Content discussed over first week (paced and reinforced) by therapist with participant and/or their carer (as available). Points to cover in discussion include:
  - i. Getting better after surgery to fix a broken hip.
    - What does 'getting better' mean to the participant and/or carer. Discuss how rehabilitation is designed to support this.
  - ii. Who is involved?
    - Focus on the participant, carer, and therapy team.
  - iii. What happens in hospital?
    - Whether their pain is appropriately managed. If related to pain, discuss usual care process for requesting pain management prior to moving/ activities. Discuss any barriers to this request and how can rectify.
    - Whether they are feeling afraid of moving/activities due concerns about falls. If so, reinforce (regularly) that this is normal but that engaging in mobility/activities as able is the best thing they can do for themselves. Provide positive feedback on moving/activity achievements at regular intervals.
    - Whether the participant's ability to think or remember clearly is different since their operation. If concerns, explore and relay findings to multidisciplinary team.
    - Why it is important for them to do as much as they can for themselves safely in hospital. Discuss need to reinforce what is completed during supervised sessions in their own time (if therapist deems it safe to do so).
    - Discharge planning and whether the participant and/or carer feels they are involved in decision making. If not, why not, and how can rectify.
  - iv. What happens after hospital?
    - Discuss likely care pathway including waiting times.
    - Discuss what they can be doing for themselves while they wait.
  - v. What about later?
    - Manage expectations for the likely extent of therapy input once discharged from hospital and need to consider engagement with other services including charities to continue their recovery.

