### 7.7.3 High risk subgroup

*Anticipate up to 2 hours 45mins therapist time above usual care per participant.*

[figure not shown]

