## 10 ASSESSMENT OF SAFETY

Participant safety will be determined through the reporting of AE and SAE which will be coded in MedDRA. The period for AE reporting will be following the signing of the study consent form until final follow-up at 12-weeks.

**An adverse event (AE)** is defined as any untoward medical occurrence in a study participant, which does not necessarily have a causal relationship with the trial intervention. Adverse events that will be collected and reported in this trial are limited to:

1. an exacerbation of a pre-existing illness.
2. an increase in the frequency or intensity of a pre-existing episodic event or condition.
3. continuous persistent disease or a symptom present at baseline that worsens following administration of the trial intervention.

**A serious adverse event (SAE)** is defined as an untoward occurrence that:

1. results in death.
2. is life threatening (at the time of the event).
3. requires unplanned hospitalisation or prolongation of existing hospitalisation.
4. results in persistent or significant disability or incapacity.
5. Other 'important medical events' may also be considered serious if they jeopardise the participant or require an intervention to prevent one of the above consequences.
6. Results in a congenital anomaly or birth defect

NOTE: The term "life-threatening" in the definition of "serious" refers to an event in which the participant was at risk of death at the time of the event; it does not refer to an event which hypothetically might have caused death if it were more severe.

All deaths occurring from randomisation until final follow-up (12-weeks) or withdrawal from the study, irrespective of their relationship to the intervention, will be documented by a notification of death form and entered into the trial database within 24 hours of identifying the death. Cause of death will be recorded where available.

For the current intervention, prolongation of existing hospitalisation following a fall may be an expected SAE and related to the intervention, given the intervention encourages people to increase their exercise, mobility, and/or activities of daily living. A related and unexpected SAE is an event which is related to the intervention; and 'unexpected' – that is, the type of event is not listed in the protocol as an expected occurrence.

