Where AEs/SAEs occur, the team (direct care team delivering the intervention and control arms) will follow Good Clinical Practice Guidelines for the reporting to the medical team responsible for the participant's care and notify the Principal Investigator (PI). PIs at all sites will report all AEs/SAEs to the CI via the study electronic database (REDCap). The CI will review all AEs/SAEs against GSTFTs guide for assessment of whether the event is related

to the intervention or not. The CI will then be responsible for reporting SAEs to the Sponsors R&D office.

All SAEs that are to be reported to the R&D office will be signed and dated and completed by the CI. Where a related and expected SAE occurs that does not require immediate reporting, this SAE will be reported in the Annual Progress Report and copied to the R&D office, alongside any AEs that occur that are not classified as 'serious'.

Related and unexpected SAEs will be reported immediately upon knowledge of the event to the R&D office and always within 24 hours. Reports of related and unexpected SAEs will be submitted to the Main NHS/ HSC REC within 15 days of the Chief Investigator becoming aware of the event, using the appropriate template. The form will be completed in typescript and signed by the Chief Investigator. The main REC will acknowledge receipt of safety reports within 30 days. A copy of the SAE notification and acknowledgement receipt will also be sent to the R&D office. The SAE will also be documented as unexpected and related in the CRF, participants medical notes if they are in hospital at the time, annual report (with site copied), and on Datix.

A joint Trial Steering and Data Monitoring Committee (TSDMC) will be informed of the number, nature and review outcomes for all serious adverse events and be asked to recommend any necessary actions.

Where an SAE occurs that does not require immediate reporting, this SAE will be reported in the Annual Progress Report and copied to the R&D office, alongside any AEs that occur that are not classified as 'serious'. The final report will detail the number (events and individuals) and nature of all events (AEs and SAEs) reported to members of each site and/or research team and will be submitted to the REC with the sponsor copied.

Please see Appendix 1 and 2 for further information on reporting of SAEs.

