## **14 STATISTICAL CONSIDERATIONS**

### **14.1 *Sample size***

The sample size was determined in consultation with the trial statistician. The recruitment target of 60 participants aims to have sufficient participants to provide the operational experience to plan a definitive trial; provide reasonably robust estimates of our feasibility outcomes; and to estimate the variability of the proposed patient outcomes to inform a future sample size calculation. A recruitment target of 60 participants (30 per treatment arm) will allow overall retention rate at 12-weeks to be estimated with precision of  $\pm 11\%$ , using an exact 95% confidence interval, from previously observed retention rates of  $\sim 80\%$  for the same population. Assuming a non-differential retention rate of 80% at 12-week follow-up, this target will provide follow-up outcome data on  $\sim 24$  participants per arm.

This required sample size will be attainable in practice. In 2022, 255 patients were admitted to a hospital ward at St Thomas's Hospital with hip fracture. Previous trials of patients with hip fracture reported recruitment rates of 32% in hospital.

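### In-hospital non-serious symptom AEs are expected to be detected more often in the intervention arm even if harms are equal, and the AE record does not capture how each event was found

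*Protocol*

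**What the plan says.** Protocol section 7.7 gives controls usual physiotherapy and occupational therapy. The intervention arm gets the same plus a subgroup-specific package. The extra therapist time is put at 1 h 40 min for low risk (7.7.1) and 2 h 15 min for medium risk (7.7.2). For high risk, 7.7.3 says "Anticipate up to 2 hours 45mins therapist time above usual care per participant".

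Each package includes symptom enquiry:

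- **Low risk, 7.7.1 a):** a self-efficacy scale covering fatigue, pain, distress and other symptoms, with encouragement to keep reporting symptoms to the direct care team.
- **Medium and high risk, Education in 7.7.2 and 7.7.3:** discussion of pain, fear of falling, and altered thinking or memory since surgery. On the last of these the instruction is "If concerns, explore and relay findings to multidisciplinary team".
- **High risk, 7.7.3 c):** "Assessment of pain with the Algoplus dementia friendly pain scale from the first therapist contact and all contacts going forward", plus a depression scale for those with no prior depression diagnosis.

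Section 10 limits recorded AEs to three kinds of worsening of something already present, for example "an increase in the frequency or intensity of a pre-existing episodic event or condition". On reporting, it says "the team (direct care team delivering the intervention and control arms) will follow Good Clinical Practice Guidelines". Section 7.4 has the clinical team told the allocation. Section 7.5 blinds the AE/SAE assessor. Section 7.6 also collects AEs and SAEs at intervention end and at 12 weeks. Counting AEs and SAEs is secondary objective 6 in section 4.

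**The concern.** An AE count reflects both how often events happen and how often someone looks for them. During the stay, the second factor differs by arm by design. The intervention-arm team spends longer with each participant, asks about symptoms in a structured way, and is also the team that reports. Blind assessment acts only on events already reported, so it cannot restore a control-arm event that nobody asked about.

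What is at stake is interpretation. Section 10 relies on this reporting to determine participant safety, and the Trial Steering and Data Monitoring Committee (TSDMC) is asked to recommend action on SAEs and monitors safety reporting. The intervention encourages more exercise and mobility, and section 10 already anticipates related falls. An excess of minor symptom events could therefore be read as harm when part of it is surveillance, and could shape the definitive trial's safety plan.

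**Working it through.** **Figures in the protocol.** It states no AE rate, detection rate or usual-care contact time, so there is no AE figure to reproduce. Its one sample-size figure, in 14.1, is retention precision of ±11%. The exact 95% interval for 48/60 is 67.7% to 89.2%, a half-width of 10.8 points, which agrees. The point here uses only the 30 per arm.

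**Extra contact.** With the target of 20 per subgroup (7.2) and 1:1 allocation, about 10 per subgroup are in the intervention arm.

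- Mean extra time = (100 + 135 + 165)/3 = 133 minutes per intervention participant.
- Arm total = 10 × (100 + 135 + 165)/60 = 67 hours, against none above usual care in controls.
- The high-risk figure is an upper limit, and part of the time goes on exercise teaching, goal setting, discharge templates and carer training rather than symptom enquiry.

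**Effect on counts under equal harm.** The following inputs are assumptions, not protocol figures:

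- λ = true in-hospital AEs per participant, 0.5 or 1.0, the same in both arms.
- d = probability that the treating team detects an event, by arm.
- r = probability that an event missed in hospital is picked up by the intervention-end enquiry, the same in both arms.

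Expected recorded count per arm = 30 × λ × [1 − (1 − d)(1 − r)]. The ratio between arms does not depend on λ. P(I > C) is the chance that the intervention count exceeds the control count, with Poisson counts.

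| d, control vs intervention | r | Recorded share, control | Recorded share, intervention | Ratio | P(I > C), λ = 0.5 | P(I > C), λ = 1.0 |
|---|---|---|---|---|---|---|
| 0.50 vs 0.60 | 0 | 0.50 | 0.60 | 1.20 | 0.60 | 0.67 |
| 0.50 vs 0.60 | 0.5 | 0.75 | 0.80 | 1.07 | 0.52 | 0.56 |
| 0.50 vs 0.60 | 0.8 | 0.90 | 0.92 | 1.02 | 0.48 | 0.51 |
| 0.50 vs 0.75 | 0 | 0.50 | 0.75 | 1.50 | 0.77 | 0.87 |
| 0.50 vs 0.75 | 0.5 | 0.75 | 0.875 | 1.17 | 0.61 | 0.68 |
| 0.50 vs 0.75 | 0.8 | 0.90 | 0.95 | 1.06 | 0.52 | 0.55 |

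With equal detection, P(I > C) is 0.45 to 0.47, because ties are possible. The expected shift is upward whenever detection is better in the intervention arm. Its size runs from negligible to about 50%, depending on inputs the documents do not give. It shrinks quickly as the intervention-end enquiry recovers missed events.

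**The case against.** Much of the case on the other side stands.

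- **Symmetric safeguards exist.** AEs are collected from both arms at intervention end and 12 weeks (7.6). Usual-care therapists are trained in AE and SAE reporting (7.8). Treatment logs follow each therapist contact in both arms (7.7). These reduce the imbalance but do not remove it, and nothing in the protocol requires events from the scheduled enquiries to be told apart from treating-team reports.
- **The enquiry does not map neatly onto the AE definition.** The depression scale goes only to those without a prior diagnosis, so it mainly finds new problems. A change in thinking since surgery may predate trial baseline. Relaying a concern to colleagues is not filing an AE. The every-contact pain score covers only about 10 of 30 intervention participants. Worsening pain can still qualify.
- **No by-arm AE comparison is stated.** Section 14.3 describes none, and no progression criterion in 14.4 uses AEs. Tabulation may properly sit in the SAP. How an event was found is different, because it must be captured at the time.

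A reader might infer that intervention-arm counts are bound to be higher. The documents do not support that. The direction is an expectation, and with 30 per arm the observed order is uncertain, as the table shows.

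A reader might also scale the bias by contact time. Assuming 4 to 10 hours of usual therapy, 133 minutes is 56% to 22% more contact, so 36% to 18% of therapist-detected events would come only from the extra time (ratio/(1 + ratio)). The hours and the proportionality are both assumptions, and the calculation ignores recovery at intervention end, so it cannot be offered as an estimate.

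Finally, it is tempting to base by-arm counts only on sources common to both arms. That would drop events first seen in Stratify sessions, possibly including the related falls that section 10 anticipates, and would bias towards apparent safety.

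**Conclusion.** The point holds in a limited form. In-hospital detection of non-serious, symptom-type AEs is unequal by design, and the expected direction is upward in the intervention arm under equal harm. This rests on three features of the protocol: extra contact and structured enquiry in one arm only, reporting by a treating team that knows the allocation, and an AE definition built on worsening of existing conditions or symptoms.

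The size cannot be established from the documents. The ratios of 1.02 to 1.50 are illustrations under assumed detection and recovery rates. Deaths and most SAEs are little affected. The consequence is confined to a descriptive secondary objective. The change is worth making because it is cheap and the information is lost if it is not collected prospectively.

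**What to change.** 1. Add a detection-source field to the AE record, allowing more than one source: usual-care contact or notes; scheduled intervention-end or 12-week enquiry; Stratify session or assessment; observation, diary or interview.
2. Hold the field where the blinded AE assessor cannot see it, because a Stratify source reveals the allocation. The REDCap database in section 12.2 whose users are not blind is one candidate, provided the assessor has no access to it.
3. State in sections 10 and 14.3 that any by-arm AE or SAE summary shows the all-source count as the main figure, with the count from sources common to both arms beside it. The scheduled enquiry is the cleanest comparison.
4. State that the TSDMC continues to see all events, and leave expedited reporting unchanged.

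The cost is one categorical field and one extra row per AE table. The common-source count is a sensitivity view only: it can undercount intervention-arm events first found in Stratify sessions, and should be labelled so.

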#### **d) Goal-orientated activities of daily living training programme**

1. Collaborative (participant /carer and therapist) activity of daily living goal setting. Example of activity of daily living goal domains include (but are not limited to) bathing, grooming, dressing, continence, toilet use, transfers, mobility, stairs. It should be determined what 'outcome goal' is to be achieved by the point of discharge and what intermediate 'behaviour goals' are needed to achieve this goal (See Box 4 for example).

|                                                                                   |                                                                                                                                                           |
|-----------------------------------------------------------------------------------|-----------------------------------------------------------------------------------------------------------------------------------------------------------|
| Box 4: Example of outcome goal and behaviour goal needed to achieve outcome goal. |                                                                                                                                                           |
| Outcome goal                                                                      | With verbal direction and provision of a soaped sponge, I can wash myself in a seated shower chair by the time I am leaving the hospital.                 |
| Behaviour goals                                                                   | In a seated position, reach down to touch toes following verbal direction                                                                                 |
|                                                                                   | In a seated position, lift left thigh without use of hands and hold for 5 seconds following verbal direction, repeat for right thigh                      |
|                                                                                   | In a seated position, lean forward and twist around to left to touch buttocks and hold for 5 seconds following verbal direction, repeat twisting to right |
|                                                                                   | Raise left arm and hold over head, repeat for right arm                                                                                                   |

2. Up to three activity of daily living training sessions with progressions and aids (as needed e.g., reaching aid, bed rail, raised toilet seat) (See Box 5 for example of progressions).

| Box 5: Example of progressions towards behaviour goal                                                          |                                                                                                                                      |
|----------------------------------------------------------------------------------------------------------------|--------------------------------------------------------------------------------------------------------------------------------------|
| Behaviour goal                                                                                                 | In a seated position, lift left thigh without use of hands and hold for 5 seconds following verbal direction, repeat for right thigh |
| Progressions
towards goal [figure not shown] | In a seated position, lift left thigh and hold without use of hands for 3 seconds following verbal direction, repeat for right thigh |
|                                                                                                                | In a seated position, lift left thigh and hold without use of hands for 1 seconds following verbal direction, repeat for right thigh |
|                                                                                                                | In a seated position, lift left thigh and lower with control without use of hands following verbal direction, repeat for right thigh |
|                                                                                                                | In a seated position, lift left thigh without use of hands following verbal direction, repeat for right thigh                        |

3. Progress charts template completed and placed at bedside indicating to the participant what they can complete independently and/or what they should be supported by team (including carer) to complete.
4. Carers (as available)
  - i. training in the practical skills required to support safe practice of behaviour goals identified. The training will be delivered in person by a therapist on a one-to-one basis, last 30-minutes, and be tailored to the behaviour goals set. The carer will have the opportunity to practice supporting safe training towards a behaviour goal in the presence of the therapist, who will answer any questions that may arise.
  - ii. review of progress charts. A therapist will show the carer the participants progress chart which is placed at the participant's bedside (see '3' above). In particular, they will ensure the carer is able to identify behaviour goals which they
    - can practice with the participant when they visit and
    - should not practice with the participant when they visit.
The therapist will also ensure the carer understands to approach a member of the therapy team if they are not sure how to support a behaviour goal, or if they do not feel comfortable to do so.

